### 2.10.5 Health-related Quality of Life

###

Patient’s health-related quality of life will be assessed using a validated World Health Organization Quality of Life Assessment: Brief Version (WHOQOL-BREF)(The WHOQOL Group, 1998; Hasanah, 2003). It consists of 26 items which represent four domains of psychological, social relationship, environmental, physical health domains and two facets of overall quality of life and general health. The question scores of all 26 items ranged from 1 to 5.

WHOQOL-BREF has been found to be comparable to the WHOQOL-100 and other WHOQOL (The WHOQOL Group, 1998; Hasanah, 2003). It is able to discriminate between patients and healthy people in revealing characteristic impairment of certain illness, including diabetes (Hasanah, 2003). The English or Malay versions of this instrument have been validated in Malaysia (Hasanah, 2003; Chew, Mohd-Sidek & Sharif-Ghazali, 2015). The Cronbach’s alphas coefficient of the WHOQOL-BREF was found to be satisfactory, ranging from 0.66 to 0.84 (WHO, 1998; Hasanah, 2003; Chew, Mohd-Sidek & Sharif-Ghazali, 2015).

### 2.10.6 Safety

###

Safety or adverse event suspected related to the treatment, through the symptoms reported by the patients, and observations by researcher at every visit will be collected. Adverse event is defined as any unfavorable and unintended sign, symptom, or disease temporally associated with the use of a medical treatment or procedure that may or may not be considered related to the medical treatment or procedure. It will be recorded on case record form according to terms of intensity: grade 1- mild; asymptomatic or mild symptoms; clinical or diagnostic observations only; intervention not indicated; grade 2- moderate; minimal, local or noninvasive intervention indicated; grade 3- severe or medically significant but not immediately life-threatening; hospitalization or prolongation of hospitalization indicated; disabling; grade 4- life-threatening consequences; urgent intervention indicated and grade 5- death related to adverse event (NCI, 2017)**.** Nonetheless, the patients and institution will be covered by insurance or indemnify against claims arising from the trial.

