### 1.2.2 Specific Objectives:

1. To compare
2. Socio-demographic background (age, gender, ethnicity, marital status, levels of education, employment, personal income);
3. Clinical characteristics (duration of disease, glycemic control, family history of disease)
4. Physical examinations (body weight, body mass index (BMI) and waist circumference (WC)

between acupuncture and control groups at baseline.

1. To examine the effect of acupuncture towards change in the HOMA-IR and/or HRQoL within and between acupuncture and control groups after treatment.
2. To identify the presence of adverse event in patients with T2DM between acupuncture and control groups.

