## 1.4 Research Framework

This study intended to investigate the effect of acupuncture treatments on HOMA-IR and HRQoL of T2DM patients in Malaysia context. The effectiveness of the intervention will be examined through the change in HOMA-IR and/or HRQoL within and between the acupuncture and control groups after treatment. Consequently, the safety of acupuncture treatment will be identified between the acupuncture and control groups. A total of 10 sessions of acupuncture or placebo treatment will be provided to the intervention and control groups. Both groups will continue with their routine diabetes care. The primary outcome is the change of HOMA-IR while the secondary outcome is the change in HRQoL among two intervention groups. Figure 1 shows the treatments and variables to be investigated in this study.

**
[figure not shown]
**

**Figure1:** Research Framework

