## 2.7 Interventions

Subjects will receive ten sessions of real or placebo acupuncture treatment using press needle (PYONEX; 0.2 mm x 1.5 mm made by SEIRIN Corporation) over six weeks. Treatments will be administered by 3 qualified TCM practitioners or acupuncturists. They are required to undergo an intensive training to ensure consistency of the administered intervention. A standard operation procedure will be provided during the training such as identification of the acupoint location, compulsory acupoints to be used in each session, technique in performing the study treatment and the time to press needles after insertion of the needles. They will also be briefed about risk management of the trial during the training. To ensure the practitioners are masked to the group allocation, practitioners are requested not to check for the presence of a sharp tip below the plaster during the intervention***.***

Treatments will be performed twice in a week; however, a once-a-week treatment to a three-times-a-week treatment is permitted, but ten treatments must be completed within six weeks. After all the Pyonex press needles are fixed, acupuncture points will be pressed for at least three times (at 0, 15 and 30 minutes) for about 30 seconds, with the degree that can be tolerated by the subject. The follow-up for any adverse event occurs will be 1 week and the total study period will be 7 weeks. For those who are under lifestyle modification or drug treatment during intervention, they are informed to continue with their existing treatment regimens. Any medication and doses received by the participants will be recorded and monitored during the course of the study to ensure the medications are maintained throughout the study. Subjects are also advised to notify the acupuncturist immediately if there are any changes in their current treatments/circumstances such as personal details, medication or get pregnant (for woman) during the study. Safety or adverse event in each session will also be recorded.

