All subjects are required to take supine position during the treatments. New, disposable, sterilized, stainless-steel press needles will be utilized and inserted according to the acupuncture point selection sequence. The acupuncture points are disinfected with a 70% isopropyl alcohol cotton. In this study, an irradiating needling sensation (*de qi*) does not have to be achieved. “De qi” is a tingling, numbness, and heaviness feelings that occur after an acupuncture needle has been inserted in the body (National Cancer Institute [NCI], 2017). Unnecessary talking in the treatment room is also avoided***.*** During the 45 minutes needle retention period, subject’s abdomen will be covered to prevent exposure. If the subjects are not fit on that day, they will not be given any treatment and will be requested to come on other day. Similarly, if subject reports discomfort or encounter any adverse effect during intervention, acupuncture therapy will be discontinued and the treatment for that particular session will not be included.

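### Protocol Section 2.10.6 contradicts itself on which adverse events are collected: suspected-related events in one sentence, events regardless of relatedness in the next

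*Protocol*

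**What the plan says.** Section 2.10.6 of the protocol opens with the collection rule, which takes in "Safety or adverse event suspected related to the treatment, through the symptoms reported by the patients" together with what the researcher notes at each visit. The sentence that follows defines an adverse event as an unfavourable and unintended occurrence "temporally associated with the use of a medical treatment or procedure that may or may not be considered related to the medical treatment or procedure". The section then has the event entered on the case record form by grade of intensity. It describes no separate causality rating, does not name who decides whether an event is suspected to be related, and gives no rule for events judged unrelated.

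Elsewhere the protocol mentions safety recording without a relatedness condition. Section 2.7 states "Safety or adverse event in each session will also be recorded" and sets a one-week follow-up for *any* adverse event. Section 4 has safety information gathered at every session and assessed at week 7.

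Safety by group is a stated aim. The third specific objective in Section 1.2.2 is "To identify the presence of adverse event in patients with T2DM between acupuncture and control groups", and Section 1.4 repeats that "the safety of acupuncture treatment will be identified between the acupuncture and control groups".

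**The concern.** The collection rule and the definition are consecutive sentences, and they produce different data. Under the definition, relatedness is irrelevant to whether something is an adverse event. Under the collection rule, suspected relatedness is the condition for entering the data at all.

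That matters in this population. Participants have type 2 diabetes and take oral agents (Section 2.5), so a glycaemic symptom can easily be put down to the disease or the medication and never written down. A group comparison built on such a record describes only the events that someone chose to attribute to treatment. The loss is also permanent: a statistical analysis plan can choose how to tabulate events, but it cannot recover events that never reached the case record form. This makes it a protocol matter and not an analysis detail that can be left for later.

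**Working it through.** The protocol gives no safety figure to reproduce, so the check is to set the statements side by side.

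| Place in protocol | What it covers | Relatedness condition? |
| --- | --- | --- |
| 2.10.6, collection sentence | symptoms reported by patients and researcher observations, every visit | Yes: suspected related |
| 2.10.6, definition | events associated in time with treatment | No: explicitly either way |
| 2.10.6, recording sentence | *it*, graded by intensity | Depends on what *it* refers to |
| 2.7, follow-up and per-session recording | any adverse event; each session | No |
| 3, decoding | any serious adverse event | No |
| 4, data collection | safety information, every session | No |
| 1.2.2 and 1.4, objective | adverse events and safety by group | No |

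Step 1. Take an event that occurs during treatment and that nobody suspects is related. By the definition it is an adverse event. By the collection sentence it is not collected. A site cannot satisfy both sentences for this event, so the contradiction is real and does not depend on interpreting other sections.

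Step 2. See which sentence the rest of the protocol supports. Sections 2.7 and 4, and the decoding rule in Section 3, carry no relatedness condition. They agree with the definition, so the collection phrase stands alone.

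Step 3. Work out the effect if the collection phrase is followed. For a given kind of event, let pA and pC be the true proportions of patients affected in the acupuncture and control arms, and let s be the probability that such an event is suspected to be related and so recorded. Section 2.2 masks patients and practitioner, and Section 2.6 conceals allocation from researchers, subjects, acupuncturists and laboratory personnel. With masking intact, s does not depend on arm. The recorded proportions are then about s × pA and s × pC. The recorded difference is s × (pA − pC), which is smaller than the true difference in absolute size whenever s < 1; the ratio pA / pC is unchanged. This is under-counting in both arms. If masking fails, s can become sA and sC, and the recorded difference sA × pA − sC × pC can move in either direction.

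Step 4. Size. The documents give no value for pA, pC or s, and no safety threshold against which a shortfall could be judged. No numerical magnitude follows from them.

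**The case against.** The best defence is that this is one loose phrase in a protocol that otherwise points the right way. Sections 2.7 and 4 are unqualified, and within Section 2.10.6 the recording sentence follows directly after the broad definition, so its pronoun can be read as referring to events of every kind. That is fair. A reader might infer that the protocol as a whole records only related events; it does not say so, and some sites may record everything. But the phrase sits in the dedicated safety section and is the explicit statement of what is collected. The other sections leave the protocol inconsistent; they do not settle which rule a site follows.

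Three further inferences are tempting and are not supported.

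- *The filter biases the comparison between arms.* With patients, practitioners and researchers masked, this needs masking to fail, and nothing in the protocol shows that it will.
- *Events in stopped sessions are lost.* Section 2.7.1 says that, after discomfort or an adverse effect, "the treatment for that particular session will not be included". Its subject is the treatment, and the natural reading is that the session does not count towards the ten. It does not say that the event is dropped, and Section 2.7 requires recording in each session. A clarifying sentence would help, but this is not evidence of a distorted safety record.
- *With 30 per arm, losing a few events decides the safety conclusion.* The protocol sets no threshold that a few events could cross, and any event rate used to show it would be invented.

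It is also fair that the case record form (Appendix C) is not shown and may already hold a relatedness item, and that the protocol's safety aim is an objective without a named test. Neither point removes the contradiction over which events are to be collected.

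**Conclusion.** The concern holds as an internal contradiction in Section 2.10.6, with the collection phrase as the outlier against the definition and against Sections 2.7 and 4. If the phrase is followed, events judged unrelated go unrecorded and the safety objective in Sections 1.2.2 and 1.4 rests on a subjective, blinded filter. The expected consequence is an under-count in both arms, of a size the documents do not allow to be stated. This conclusion assumes that some sites will follow the phrase as written and that masking holds. It is a modest point, worth correcting because the omission cannot be repaired after data collection and the correction is simple.

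**What to change.** In Section 2.10.6, replace the phrase that limits collection to suspected-related events with wording such as: *all adverse events that meet the definition below, whether or not a relationship to treatment is suspected*. Add that the relatedness judgement, made blind to allocation, is a separate item on the case record form next to the intensity grade, if the form does not already have one. Check that Sections 2.7 and 4 read consistently with this.

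Optionally, add a sentence to Section 2.7.1 saying that the exclusion of a stopped session refers to the count of ten sessions, and that any event in it stays in the safety data.

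The cost is one changed phrase, one or two added sentences, at most one form item, and a few more minor events to record.

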# 3. Early termination, drop-outs, withdrawal and decoding procedure

Early termination of the trial is allowed if the risks are found to outweigh the potential benefits, if there is any serious adverse event that cause by the trial or when there is conclusive proof of positive and beneficial results. In the event that subject does not turn up for treatment or assessment, they are invited to join the other subsequent session. Subject’s is considered drop-outs if they have missed their appointments for more than three times, they do not attend the baseline or assessment session (cause missing data), they become pregnant (for women), withdrawal of his/her own decision or advised by the researcher (for example increase 20% doses of diabetes medication or using acupuncture at other clinic during intervention). Additionally, withdrawal subject will be followed up until the end of the study and every effort must be made to report the observation. Last but not least, decoding procedure shall undertake if there is any serious adverse event occurred.

# 4. Data Collection

The research will be undertaken from 2021 until 2022. Subject’s socio-demographics and clinical characteristics are obtained during baseline visit. HOMA-IR, HRQoL, body weight, height, BMI and WC will be collected at baseline and at week 7 after intervention. However, safety information will be collected at every session and assessed at week 7 after the trial.

# 5. Statistical Analysis

Data will be analyzed using SPSS Statistics 26.0 (IBM Corp., New York, USA). Data will be presented as mean ± SD for continuous parameters and percentage for categorical data. Kolmogoro-Smirnov tests for normality will be performed on each parameter before analysis. Comparisons of background and baseline continuous variables between intervention and control group will be examined using independent t-test, while for categorical variables the chi-square test will be used. Intention-to-treat analysis (ITT) will be performed, and all patients enrolled will be included in the analysis, irrespective of compliance. The missing data is imputed using last observation carried forward method. Paired t-test will be carried out in analyzing the statistical significance of mean pre-post change in the parameters. The changes between groups on two time-points (pre-post) will be conducted using analysis of covariance (ANCOVA) if covariates are present. A repeated measure ANCOVA is performed to compare changes between groups at baseline, week 3/4 (6^th^ visit) and week 7 of intervention while controlling for a confounding variable. Mc Nemar’s test is utilized for matched pair’s comparison. However, if data are not normally distributed, non-parametric tests are used. The significant level for all tests is set at p<0.05 (two-tailed).

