## 2.4 Sample Size

The sample size calculation is based on previous study (Firouzjaei et al. 2016) where the mean differences of HOMA-IR and standard deviation between two groups were 1.23 and 1.25 respectively. For the mean comparison method of two-sample t-test model, a significance level of 5% z_(1-∂/2)_ = 1.96 and a power of 90% z_(1-ß)_ = 1.28 will be utilized to calculate the required sample size.

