## 2.10 Measurements

Measurements are performed at baseline and week 7 of the study. A case record form (CRF) will be developed to ascertain socio-demographics, clinical characteristics, physical examinations and HRQoL information of the participants (Appendix C).

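### With HOMA-IR scheduled only at baseline and week 7, last observation carried forward records a change of exactly zero for every patient who has no week 7 value

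*Protocol*

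**What the plan says.** - **Outcome.** Section 1.4: "The primary outcome is the change of HOMA-IR"; quality of life is secondary.
- **Schedule.** Section 2.10: "Measurements are performed at baseline and week 7 of the study". Section 4 repeats these two times for HOMA-IR and quality of life by name.
- **Missing values.** Section 5: "The missing data is imputed using last observation carried forward method". It names no other method and no sensitivity analysis. The same section calls for intention-to-treat analysis of all enrolled patients regardless of compliance.
- **A third time point.** Section 5 also describes a repeated-measures ANCOVA at baseline, week 3/4 and week 7. It does not say which parameter is measured at week 3/4, and sections 2.10 and 4 schedule nothing then.
- **Drop-outs.** Section 3 counts as drop-outs, among others, patients withdrawn on the researcher's advice, with the example "increase 20% doses of diabetes medication or using acupuncture at other clinic during intervention". It adds that "withdrawal subject will be followed up until the end of the study and every effort must be made to report the observation".
- **Expected loss.** Section 2.4 allows for 35% drop-out and sets 30 patients per group.

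**The concern.** Carrying a value forward assumes that the outcome would have stayed at its last observed level. When the only earlier value is the baseline, this amounts to assuming that the patient did not respond at all. For an outcome defined as change, the rule writes in a zero.

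Three consequences follow:

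- If acupuncture lowers HOMA-IR, the zeros dilute the estimated effect.
- Each zero counts as a measured patient, so the analysis claims information from 30 per arm when fewer were observed.
- If both arms change for reasons other than the needles and drop-out differs by arm, the arm with more zeros appears to change less. That creates a difference where there is none.

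The within-group paired t-tests use the same zeros. With up to about a third of patients expected to be lost, this bears directly on the primary result.

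**Working it through.** **Inputs.** Section 2.4: "the mean differences of HOMA-IR and standard deviation between two groups were 1.23 and 1.25 respectively"; 5% significance (z = 1.96), 90% power (z = 1.28), 35% drop-out, 30 per group. Section 5 confirms two-sided testing. Assumptions, because the protocol does not settle them: 1.25 is the SD of the change, the mean change in controls is 0, and drop-out is unrelated to outcome. The analysis checked is an unadjusted comparison of mean change, with differences given as magnitudes.

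**The plan's own figure.** n = 2 × (1.96 + 1.28)² × 1.25² / 1.23² = 21.68, so 22 per group, as stated. The 30 per group is 22 × 1.35 = 29.7. At 35% drop-out, 30 × 0.65 = 19.5 per group are observed, fewer than 22.

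**Carrying baseline forward, drop-out share d in both arms.** The expected difference is (1 − d) × 1.23. The variance of change in an arm with mean change m is (1 − d) × 1.25² + d(1 − d) × m².

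At d = 0.35:
- Difference: 0.65 × 1.23 = 0.80, a bias of −0.43 (−35%).
- Active-arm variance: 0.65 × 1.5625 + 0.35 × 0.65 × 1.5129 = 1.360. Control-arm variance: 0.65 × 1.5625 = 1.016.
- SE: √[(1.360 + 1.016)/30] = 0.281.
- SE from observed cases only: 1.25 × √(2/19.5) = 0.400. The carried-forward SE is about 30% smaller (1 − 0.281/0.400).
- Coverage of 1.23 by the nominal 95% interval: bias/SE = 0.4305/0.281 = 1.53, and Φ(1.96 − 1.53) − Φ(−1.96 − 1.53) ≈ 0.67. Simulation with t-tests gives about 0.66.
- Power: Φ(0.80/0.281 − 1.96) = 0.81. Observed cases: Φ(1.23/0.400 − 1.96) = 0.87 by the normal formula, about 0.84 by simulated t-tests.

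At d = 0.20:
- Difference: 0.80 × 1.23 = 0.98.
- SE: 0.30, against 0.36 for observed cases.
- Coverage: about 87%.

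**No treatment effect.** With 35% drop-out in both arms and no change in either, simulated type I error is about 5%. With unequal drop-out and a common fall m, the expected spurious difference is m × (gap in drop-out). The rates and falls below are assumptions, not protocol figures:

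| Drop-out by arm | Common fall | Spurious difference | Type I error |
|---|---|---|---|
| 35% vs 15% | 1.0 | 0.20 | about 10% |
| 35% vs 15% | 0.5 | 0.10 | about 6–7% |
| 45% vs 25% | 1.0 | 0.20 | about 11% |
| 45% vs 25% | 0.5 | 0.10 | about 7% |

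The sign depends on which arm loses more patients.

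**The case against.** Several points on the other side are sound and limit the finding.

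- **Not every drop-out gets a zero.** A reader might infer that all patients whom section 3 labels drop-outs are imputed. That section defines drop-out partly by missed appointments, medication changes or outside acupuncture, and it requires follow-up to the end of the study. Only patients without a week 7 value are affected.
- **The plan does not discard the week 7 values of withdrawn patients.** Intention-to-treat analysis with imputation of missing data only, read with the follow-up rule, already implies that an observed value is used. This needs stating, not inventing.
- **The last observation need not be baseline.** If HOMA-IR is measured at week 3/4, patients lost later would carry forward a mid-treatment value. Sections 2.10 and 4 schedule no such measurement, so the conflict is real. Patients lost before that visit would still get zero.
- **Intervals are not too narrow in every case.** The zeros raise an arm's SD above 1.25 once its mean change exceeds 1.25/√0.65 = 1.55. The SE exceeds even the observed-case value if both arms change by more than about 2.47. At the plan's own figures it is too small.
- **The fall from 90% to 81% power is not all due to this rule.** The fair comparator is 84–87%. The rest comes from drop-out itself and from inflating 22 by 1.35, where 22/0.65 gives 34.
- **Masking makes a large drop-out imbalance less likely**, and the false-positive scenarios rest on assumed figures.

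It might also be argued that the rule is conservative. With equal drop-out the bias is indeed towards zero and type I error stays near 5%, but the effect size and its precision are still misreported.

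**Conclusion.** The concern holds on the schedule that sections 2.10 and 4 fix: the rule sets the change to zero for each patient with a baseline but no week 7 value. Under the three assumptions stated, at the plan's 35% drop-out, it yields 0.80 instead of 1.23, with an SE of 0.28 against 0.40 and about 66% coverage. At 20% drop-out the figures are 0.98 and about 87%. The loss of power due to the rule is modest, about 3 to 6 points; bias and false precision are the main harm. Inflated type I error is conditional: it needs both unequal drop-out and a common change in the two arms. The protocol does not support reading it as a general result. Because this is the only missing-data rule and it acts on the primary outcome, it should be changed before the data are analysed.

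**What to change.** 1. Remove last observation carried forward as the primary method.
2. Analyse all randomised patients by ANCOVA of week 7 HOMA-IR adjusted for baseline. State that every observed week 7 value is used, including those of withdrawn patients followed under section 3. Treat quality of life the same way.
3. Handle the remaining missing values by a method valid under missing at random, for example multiple imputation using arm and baseline HOMA-IR. Add a sensitivity analysis for departures from that assumption, such as a range of shifts applied to the imputed values.
4. Replace *enrolled* with *randomised* in the definition of the analysis set. A person with no baseline value has nothing to carry forward, and section 2.6 already implies that HOMA-IR is known before allocation.
5. Reconcile the week 3/4 time point in section 5 with sections 2.10 and 4, naming what, if anything, is measured then.

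The cost is revised wording, a little more analysis work, and wider confidence intervals that reflect the data held. No new data are needed, since follow-up of withdrawn patients is already required.

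### The repeated-measures ANCOVA needs a week 3/4 outcome measurement that the protocol text does not schedule, and no between-group test is named as primary

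*Protocol*

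**What the plan says.** Section 5 (Statistical Analysis) gives two between-group analyses of the outcomes. The first is for two time points: "The changes between groups on two time-points (pre-post) will be conducted using analysis of covariance (ANCOVA) if covariates are present". The second is for three: "A repeated measure ANCOVA is performed to compare changes between groups at baseline, week 3/4" (identified as the 6th visit) and week 7, controlling for a confounder that is not named. The independent t-test in the same section is assigned to background and baseline variables, and the paired t-test to pre-post change. A non-parametric fallback is mentioned without naming the tests.

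The schedule is given twice. Section 2.10 (Measurements) states: "Measurements are performed at baseline and week 7 of the study". Section 4 (Data Collection) lists the variables: "HOMA-IR, HRQoL, body weight, height, BMI and WC will be collected at baseline and at week 7 after intervention". It then sets safety apart: "safety information will be collected at every session and assessed at week 7 after the trial".

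Section 5 also gives a rule for gaps: "The missing data is imputed using last observation carried forward method". Section 1.4 makes the change in HOMA-IR the primary outcome and the change in quality of life the secondary one.

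**The concern.** An analysis at three time points needs outcome values at all three. The text schedules none at the middle one, so Section 5 describes a model that Sections 2.10 and 4 cannot supply.

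Two things are at stake.

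- **Which test decides the trial.** The repeated-measures ANCOVA is the only named between-group outcome test that Section 5 states without a condition. The pre-post ANCOVA depends on covariates being present, and the protocol does not say what happens otherwise. Neither is called primary, and every test is run at the two-sided 0.05 level. The choice between them could therefore be made after the data are seen.
- **What imputation would do.** With last observation carried forward, whether a midpoint exists decides which value replaces a missing week 7 result. Without a midpoint it is the baseline value, so the participant contributes zero change. With one it is the week 3/4 value. Section 2.4 allows for 35% dropout, so this could touch a sizeable share of the primary data.

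**Working it through.** **The plan's own figure.** Section 2.4 gives a between-group difference of 1.23, a standard deviation of 1.25, a two-sided 5% level (1.96) and 90% power (1.28):

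n per group = 2 × (1.96 + 1.28)² × 1.25² / 1.23² = 2 × 10.4976 × 1.5625 / 1.5129 = 21.68, rounded up to 22.

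The stated 22 per group is reproduced. The formula is for a two-sample comparison of means. It has no input for a number of time points or a within-subject correlation, so the sample size neither needs nor supports a week 3/4 value.

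**Time points side by side.**

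| Source | Baseline | Week 3/4 | Week 7 |
|---|---|---|---|
| Section 5, repeated-measures ANCOVA | yes | yes | yes |
| Section 5, pre-post ANCOVA | yes | no | yes |
| Section 2.10, measurements | yes | no | yes |
| Section 4, HOMA-IR, quality of life, weight, height, BMI, waist | yes | no | yes |
| Section 4, safety | collected at every session | collected at every session | assessed |

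The repeated-measures ANCOVA needs 3 outcome time points and the schedule gives 2. The other session-level records in Sections 2.7 and 2.7.1 are medication and the acupuncture points used. No text provides a blood sample, questionnaire or body measurement at mid-course.

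**Could imputation fill the gap?** If last observation carried forward were applied mechanically to the uncollected visit, every week 3/4 value would equal that participant's baseline value. The time point would carry no information.

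**What remains runnable.** The pre-post ANCOVA uses only baseline and week 7, both of which are scheduled for HOMA-IR and quality of life.

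**Side note on timing, taking the 6th visit as the 6th treatment session.** Section 2.7 has two sessions a week as the norm and permits one to three, with the limit that "ten treatments must be completed within six weeks".

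- At two a week, session 6 falls in week 3.
- At three a week, it falls in week 2.
- With weekly counts 1, 1, 1, 1, 3, 3 (total 10), four sessions are done by the end of week 4, and session 6 falls in week 5.

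The possible range is week 2 to week 5, but the ends need unusual patterns, and the default fits the label week 3/4.

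**The case against.** The strongest reply is that a midpoint assessment may have been intended. The label of a specific visit, the 6th, suggests that someone had one in mind. The study schematic (Figure 3), the procedure flow chart (Figure 4) and the case record form (Appendix C) are not shown, and any of them might include it. This stands as a limit: one cannot say that no midpoint data will exist, only that the text schedules none. Even if a figure showed one, Sections 2.10 and 4 would still disagree with Section 5.

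A second reply is that covariate detail is commonly left to a statistical analysis plan, which is not at hand. That is fair for the list of covariates. It does not cover a time point that the protocol's own schedule omits, or a between-group test that the protocol itself makes conditional.

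Three stronger readings are tempting, and the protocol does not support them.

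- A reader might infer that entering baseline as a repeated level dilutes the treatment effect, perhaps by half. That applies to a group main effect, which Section 5 never names. Comparing changes between groups over time most naturally means the group-by-time interaction, which is not diluted in that way. Any dilution figure would also rest on an assumed midpoint effect that the protocol does not give.
- A reader might infer that the analysis departs from a week 7 change on which the trial was sized. Section 2.4 refers only to a mean difference in HOMA-IR between two groups in an earlier study. It does not say that 1.23 is a change or that it belongs to week 7.
- A reader might infer that the primary outcome cannot be analysed. The pre-post ANCOVA shows that it can.

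**Conclusion.** The point holds as an internal contradiction. On the text, one of the two named between-group outcome analyses cannot be run, because it needs three time points and the schedule supplies two. The other can be run but is conditional, and neither is designated primary. This rests on the written schedule being complete; a figure or form that is not shown could add a midpoint, in which case the sections would still need to be aligned.

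The size of the problem is best stated in those terms. No numerical bias or loss of power can be derived from the protocol, and the sample size of 22 evaluable participants per group is unaffected. The baseline and week 7 data are sound for a between-group comparison. What needs correcting is the choice and specification of the test, before any outcome data are examined. The loose timing of the 6th visit is minor and matters only if a midpoint is kept.

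**What to change.** Reconcile Sections 2.10, 4 and 5.

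**Preferred, because it adds no procedure.** Remove the week 3/4 repeated-measures ANCOVA from Section 5. Name one primary between-group analysis: week 7 HOMA-IR compared between arms by ANCOVA with baseline HOMA-IR as covariate, applied whether or not other covariates are identified. Analyse quality of life in the same way, with its own baseline score as covariate. Both baseline values are already collected. Apart from one degree of freedom, baseline adjustment should be at least as precise as an unadjusted comparison. The cost is protocol wording only, with no extra visit or blood draw.

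**If a midpoint was intended.** Add it to Sections 2.10 and 4, name the outcomes measured there, and define its timing by a window rather than by session number alone. Keep the week 7 contrast as primary and label the midpoint analysis secondary. State how last observation carried forward would use the midpoint value. This costs an additional assessment for each participant, including a fasting blood sample if HOMA-IR is one of the outcomes.
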